## Outcomes

5

The RCT is designed to evaluate the feasibility of conducting a future definitive trial. Hence, the trial's primary outcomes will be the key feasibility indicators required to recommend progression towards a future larger‐scale trial (trial recruitment, trial retention, EMDR/TF‐CBT treatment engagement, and EMDR/TF‐CBT treatment fidelity). These will be operationalised according to pre‐specified feasibility thresholds informed by past research on trauma‐focused interventions in people with first episode psychosis (Varese et al. 2024) and approved by an independent Trial Steering Committee (Table 2).

**TABLE 2 eip70095-tbl-0002:** Principal feasibility outcomes and proposed feasibility thresholds considered in the RESTART feasibility RCT.

Criterion	Critical feasibility outcome	Other feasibility and acceptability data relevant to the criterion		Proposed thresholds on critical outcome
1. Recruitment rate	Number of participants consented into the trial and randomised	Number of referrals per month Source of recruitment Number of participants contacted, number of participants assessed for eligibility Reasons for non‐eligibility or withdrawal of interest	  	Feasibility will be demonstrated where an average of at least 3 participants are recruited and randomised per month of active recruitment. If at least 2 participants are recruited per month, then a future trial will be feasible but additional strategies must be identified to support recruitment (e.g., informed by other feasibility data relevant to this criterion) If an average of 1 participant is recruited per month over the recruitment period (< 20 participants), feasibility within the current design will not be demonstrated
2. Therapy engagement	% who drop‐out of therapy/% who did not receive treatment allocated	Number of therapy sessions attended Reasons for failed initiation of treatment Reasons for premature termination of treatment Session record forms for each therapy session Analysis of characteristics of therapy engagers vs. non‐engagers Qualitative interviews with SU participants	  	Feasibility will be demonstrated if at least 70% of the participants in the intervention arm completed at least 8 sessions of EMDRp or TF‐CBTp If 50%–70% of participants in the intervention arm complete at least 8 sessions of EMDRp or TF‐CBTp, a future trial considering these intervention will be feasible but changes to the trial design or treatment protocol may be warranted to ensure deliverability (e.g., informed by other feasibility data relevant to this criterion) If less than 50% of participants in the intervention arm complete at least 8 sessions of EMDRp or TF‐CBTp, feasibility within the current design will not be demonstrated
3. Assessment retention	Percentage of participants who are lost to follow‐up	Reasons for withdrawal from the study Qualitative interviews with SU participants	  	If at least 70% of participants are retained and the 9‐month post‐randomisation assessment, feasibility will be demonstrated If 30%–70% of participants are retained at the 9‐month post‐randomisation assessment, a future trial will be feasible if strategies to overcome barriers are identified (e.g., via other data relevant to this criterion) If less than 30% of participants are retained at the 9‐month post‐randomisation assessment, feasibility within the current design will not be demonstrated
4. Therapy fidelity	Adherence ratings from therapy tapes	Session record form for each therapy session (including reasons for deviation from protocol)	  	Feasibility will be demonstrated if over 80% of rated therapy tapes will be rated as acceptable If 50%–80% of rated therapy tapes will be rated as acceptable, a future trial will be feasible if strategies to overcome identified barriers (e.g., exploring the reasons for deviation from protocol recorded in the therapist checklists) If less than 50% of rated therapy tapes will be rates as acceptable, feasibility within the current design will not be demonstrated

*Note:* Amber = continue but modify protocol—the future definitive trial is feasible with modifications; Green = continue to main study without modifications—feasible as it is. Red = stop—future definitive trial is not feasible. The feasibility thresholds below have been informed by and adapted from those employed in a past trial of trauma‐focused therapy for psychosis conducted by the Chief Investigator (the EASE trial; Varese et al. 2021; Varese et al. 2024), which were proposed/approved by the EASE trial TSC.

To evaluate the feasibility of completing the battery of measures to be employed in the future definitive trial, and gather outcome data to establish the ‘promise of efficacy’ of EMDR and TF‐CBT, participants will be assessed at baseline and 9‐months post randomisation follow‐up appointments using an assessment battery covering relevant clinical and mechanistic measures (see Table 3 for details). Additionally, at 12‐months post randomisation, participants' clinical notes will be screened to assess transition rates to first episode of psychosis and document the support received as part of TAU over the course of the trial. Additional data collection will be undertaken with all participants allocated to the TF‐CBT + TAU and EMDR+TAU arms of the trial over the course of treatment, and will include (1) sessional measures to monitor symptom fluctuations over the course of treatment (using the PQ‐16 and a sessional measure of post‐traumatic symptoms adapted from Peters et al. 2022); (2) measures of therapeutic alliance (by administering at session 3, session 12 and at therapy completion the Working Alliance Inventory—Short Form Revised; Hatcher and Gillaspy 2006); (3) a brief questionnaire to assess, at the end of treatment, the tolerance/acceptability of the psychological therapy they received (Devilly 2004).

**TABLE 3 eip70095-tbl-0003:** Summary of measures used to assess participant symptoms at baseline and follow‐up.

		Baseline	9‐months
Demographic information and clinical history			
Age, sex, ethnicity, employment status and occupation (if relevant), marital status, education level, disability status, self‐reported diagnosis, treatment history, duration of EDIT/Early Intervention service input if applicable, number and reasons for past psychiatric hospitalisations, current prescribed medications for mental health difficulties (including dosage), diagnosis.		X	Updated as required
At‐risk mental state related measures			
PQ‐16	A short measure designed to assess psychosis risk	X	X
CAARMS‐23	A semi‐structured interview to identify those at ultra‐high risk of developing psychosis	X	X
CAPE‐N	A measure to detect those who present an increased risk for developing psychosis	X	X
Trauma‐related measures			
TALE	A measure designed to assess exposure to adverse and traumatic life experiences commonly reported by people with psychosis/ARMS.	X	—
PCL‐5	A self‐report questionnaire assessing the presence and severity of PTSD symptoms	X	X
ITQ	A brief measure assessing the severity of symptoms of PTSD and complex PTSD as defined in the ICD‐11.	X	X
DSPS	A measure assessing lifetime and past month dissociative symptoms	X	X
TMQ	A questionnaire assessing the quality of the memory of the traumatic event	X	X
PTCI‐9	A brief measure assessing thoughts and beliefs related to/arising from the traumatic event	X	X
MCQ‐PTSD	A questionnaire measuring metacognitive beliefs following a traumatic experience	X	X
PTGI‐SF	A short‐form questionnaire measuring positive growth following adverse life events	X	X
Health economic measures			
EQ‐5D‐5L	A short self‐report measure assessing service users' current health	X	X
EPQ	An adapted version of the EPQ for specific use in services users with ARMS	X	X
Other mental health and functioning measures			
GAD‐7	A commonly used questionnaire assessing symptoms of anxiety.	X	X
PHQ‐9	A commonly used questionnaire assessing symptoms of depression.	X	X
CAS‐1R	A questionnaire measuring cognitive attentional syndrome and metacognitive beliefs	X	X
QRP	A questionnaire measuring aspects of recovery	X	X
AQ‐10	A short measure assessing autism‐spectrum traits	X	—
EoTT	A new questionnaire developed for this trial to assess concerns that participants may have about engaging in trauma focused interventions; an initial validation of the EoTT (e.g., internal consistency and association with other relevant measures collected as part of the trial) will be conducted using data collected as part of this feasibility RCT	X	—

*Note:* Economic Patient Questionnaire (Davies et al. 2007); AQ‐10 = Autistic Spectrum Quotient (Allison et al. 2012); CAARMS = The Comprehensive Assessment of At‐Risk Mental States (Yung et al. 2005); CAPE‐*N* = negative symptoms scale of the Community Assessment of Psychic Experiences scale (Mossaheb et al. 2012); CAS‐1R = Cognitive Attentional Syndrome Questionnaire (Faija et al. 2019); DSPS = The Dissociative Subtype of PTSD Scale (Wolf et al. 2017); EoTT = Expectations of Therapy Questionnaire (under development as part of a PhD at the University of Manchester); EPQ = Economic Patient Questionnaire (Varese et al. 2021); EQ‐5D‐5L = The EuroQol 5‐Dimension 5‐Level measure (Janssen et al. 2013); GAD‐7 = The Generalized Anxiety Disorder Questionnaire (Spitzer et al. 2006); ITQ = International Trauma Questionnaire (Cloitre et al. 2018); MCQ‐PTSD = The Metacognitions Questionnaire for Post‐Traumatic Stress (Wells 2009); PCL‐5 = The PTSD Checklist for DSM‐5 (Blevins et al. 2015); PHQ‐9 = The Patient Health Questionnaire (Kroenke et al. 2001); PQ‐16 = The 16‐items version of the Prodromal Screening Questionnaire (Ising et al. 2012); PTCI‐9 = The brief Post‐Traumatic Cognitions Inventory (Wells et al. 2019); PTGI‐SF = The Post‐Traumatic Growth Inventory short‐form (Cann et al. 2010); QPR = The Questionnaire about the Process of Recovery (Neil et al. 2009); TALE = The Trauma and Life Events checklist (Carr et al. 2018); TMQ = The Trauma Memory Questionnaire (Halligan et al. 2003).

In line with recommended practice (Health Research Authority [HRA] 2023; International Council for Harmonisation [ICH] 2016), all adverse events (AEs) experienced by participants over the course of the RCT will be monitored and assessed by a clinically qualified senior researcher to establish seriousness (i.e., those resulting in death; life‐threatening circumstances; new or prolonged hospitalisations and emergency care; persistent disability or incapacity), severity, relatedness to trial procedures/interventions, and expectedness. All suspected serious SAEs will be independently assessed by the chair of an independent trial steering committee and reported to relevant regulatory bodies. To promote active monitoring of AEs, RAs will inquire about possible serious AEs during all follow‐up assessments with trial participants and via an additional phone call 4.5 months following the end of baseline assessment. Medical notes will also be monitored up to 12 months post‐randomisation to identify any unreported AEs.

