**Method:**

Seventy ARMS individuals with a history of trauma will be randomised to receive 24 sessions of EMDR plus treatment as usual (TAU), 24 sessions of TF‐CBT+TAU, or TAU alone. Feasibility will be determined against pre‐specified thresholds for recruitment, retention, treatment engagement, and fidelity. To examine the promise of efficacy of EMDR and TF‐CBT, participants will complete a battery of clinical and mechanistic measures at baseline and 9‐month post‐randomisation, including assessments of attenuated psychotic symptoms and post‐traumatic symptoms. Clinical notes will be reviewed to identify transitions to first episode psychosis up to 12 months post‐randomisation. Qualitative interviews with trial participants, therapists, and professional stakeholders will explore the acceptability of EMDR and TF‐CBT and factors to facilitate future implementation of trauma therapies in routine practice.

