### Participants

3.2

This trial will aim to recruit 75 individuals who (1) meet ARMS criteria operationalised using the updated version of the Comprehensive Assessment of At‐Risk Mental States (CAARMS‐23; Yung et al. 2023) and (2) report exposure to past traumatic events in childhood or adulthood on the Trauma and Live Events questionnaire (TALE; Carr et al. 2018). The full inclusion and exclusion criteria of the RCT are listed in Table 1.

**TABLE 1 eip70095-tbl-0001:** Inclusion and exclusion criteria.

Inclusion criteria	16 years of age or older Meeting ARMS criteria as defined by the CAARMS Capacity and willingness to provide informed consent Reported exposure to at least one potentially traumatic life events, as assessed by the TALE
Exclusion criteria	Under 16 years of age Non‐English speaking or requiring an interpreter for the intervention (the assessment battery at present can only be delivered in English) Evidence of recent or past transition from ARMS status to first episode psychosis (FEP), operationally defined as meeting CAARMS transition criteria (i.e., history of a treated or untreated psychotic episode of 1 week's duration or longer) and/or previous or current treatment with antipsychotics at dose of over 5 mg of haloperidol or equivalent for over 3 weeks Judged by the assigned care‐coordinator/responsible clinician and the research team as not sufficiently clinically stable to engage safely in a clinical trial of trauma‐focused therapy (e.g., acutely suicidal and suicide attempt in the previous 2 months; in a current mental health crisis; not in stable housing).

*Note:* ARMS = at risk mental state; CAARMS = comprehensive assessment of at risk mental states (Yung et al. 2005); TALE = Trauma and Life Events checklist (Carr et al. 2018).

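### Table 2 gives no recruitment verdict for averages between 1 and 2 participants per month, and the participant count beside the red band does not close the gap

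*Protocol article*

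**What the plan says.** The protocol article, section 5 (Outcomes), names recruitment as one of four primary feasibility outcomes and refers to Table 2 for pre-specified thresholds approved by an independent TSC. For criterion 1, recruitment rate, the three bands are:

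- Green: "an average of at least 3 participants are recruited and randomised per month of active recruitment".
- Amber: "If at least 2 participants are recruited per month, then a future trial will be feasible but additional strategies must be identified".
- Red: "If an average of 1 participant is recruited per month over the recruitment period", followed by a bracketed count of fewer than 20 participants.

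Only the red band carries a count. The note under Table 2 defines green as going on to the main study unmodified, amber as going on with modifications, and red as stopping.

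The recruitment target appears twice. The Abstract has "Seventy ARMS individuals with a history of trauma will be randomised" and section 3.2 has "This trial will aim to recruit 75 individuals". The article does not give the length of the recruitment period.

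**The concern.** A traffic-light rule should assign a verdict to every possible result. This one defines red as a single value, 1 per month, and starts amber at 2 per month. The other three criteria in Table 2 use an open-ended red bound that meets amber: below 50% for engagement, below 30% for retention and below 50% for fidelity. Recruitment alone leaves a space between red and amber.

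If the trial recruits at, say, 1.5 per month, one reader may take red to mean anything short of amber and stop. Another may take the count of 20 as the true lower limit of amber and continue with modifications. The decision would then be made after the result is known, which pre-specified thresholds are meant to prevent.

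The count raises a second question: whether the red count, the monthly rates and the recruitment target can all refer to the same recruitment period.

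**Working it through.** **Inputs.** From Table 2, criterion 1: green at 3 or more per month, amber at 2 or more, red at 1 per month with fewer than 20 participants. From the Abstract and section 3.2: targets of 70 and 75. The recruitment length T, in months, is not stated, so it is varied. Throughout, count = rate × T.

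**1. The plan's own figure.** One per month for T months gives T participants.

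- T = 18 or 19 gives 18 or 19, which agrees with fewer than 20.
- T = 20 gives exactly 20, which misses by one.
- T = 25 gives 25, which conflicts; 20 participants would then be 20/25 = 0.8 per month.

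The gloss therefore fits its rate only if T is below 20.

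**2. The gap by rate.** Red is 1 and amber starts at 2. Any average strictly between them has no band, whatever T is.

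**3. The gap by count.** If the bracketed count is taken as the red limit, red ends at 19 and amber starts at 2T. Totals from 20 to 2T − 1 are unclassified whenever 2T exceeds 20, that is, for T above 10.

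| T (months) | Amber starts (2T) | Unclassified totals |
|---|---|---|
| 10 | 20 | none |
| 12 | 24 | 20–23 |
| 18 | 36 | 20–35 |
| 20 | 40 | 20–39 |
| 25 | 50 | 20–49 |

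At T = 10, where the gap closes, the green rate yields 3 × 10 = 30 participants, far from 70 or 75.

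**4. Can red be read as below 2 per month?** At T = 20 that would be fewer than 2 × 20 = 40 participants, but the table says fewer than 20. The count does not support this reading.

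**5. Red count against target.**

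- 1 per month being fewer than 20 needs T < 20.
- 3 per month reaching the target needs T ≥ 70/3 = 23.3 months, or T ≥ 75/3 = 25 months.

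No T satisfies both. At T = 20, green is reached with 60 participants: 60/70 = 86% or 60/75 = 80% of target.

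**6. Chance of landing in the gap.** Take T = 20 (an assumption) and let the total be Poisson with mean rate × 20. The quantity is P(20 ≤ X ≤ 39).

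| True rate per month | Mean total | P(unclassified) |
|---|---|---|
| 1.5 | 30 | 0.93 |
| 2 | 40 | 0.48 |
| 2.5 | 50 | 0.06 |
| 3 | 60 | 0.0025 |

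At 1.5 per month the result is similar for other lengths: 0.88 at T = 18 (totals 20–35) and 0.97 at T = 25 (totals 20–49).

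**The case against.** The strongest reply is that much of this turns on a recruitment length that a condensed article may properly leave to the full protocol. That holds for the match between count and rate. A reader might infer that 1 per month and fewer than 20 participants plainly disagree, but the article does not show this: they agree at 18 or 19 months and differ by one participant at 20.

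A reader might also infer that green is wrong because it can be met while missing the target. That is not supported either. Green is a rate judged adequate for a future trial, 75 is what this trial aims for, and nothing in the article says the two must coincide. A green cut below the target is a permissible choice.

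Nor do the three wordings of the denominator (months of active recruitment, months, and the recruitment period) show a real conflict. They read naturally as shorthand for one thing.

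The 93% assumes a true rate at the centre of the gap, for which the article gives no evidence. It should be read only with the rest of the range.

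Finally, section 7 says that qualitative findings also inform the progression decision, so Table 2 is not the only input. That softens the consequence but does not supply the missing verdict. The gap itself stands: it lies in what Table 2 states, and it needs no assumption about T.

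**Conclusion.** The recruitment criterion is wrong as written. Averages above 1 and below 2 per month have no verdict, and by count 20 to 2T − 1 participants are unclassified for any recruitment longer than 10 months. The same result could be called stop or continue with modifications. This rests only on the wording of Table 2.

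Two further statements need qualification:

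- **Red count and target.** The red count and a green rate that delivers 70 or 75 cannot both hold for any one recruitment length. Either the count does not match its rate, or green sits below the target. The article does not show which, and the second would be acceptable if stated.
- **Size.** The probabilities assume Poisson recruitment and, in the main table, 20 months. The gap is likely to matter if true recruitment is near 1.5 to 2 per month, and hardly at all if it is near 3.

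In the engagement and retention rows, exactly 70% falls in both green and amber. Because green is worded to include 70%, this is an editorial matter only.

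**What to change.** Before recruitment data are reviewed, the TSC should approve a reworded criterion 1 that does three things:

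1. **Makes the bands contiguous.** One option is red below 2 per month, amber from 2 to below 3, and green at 3 or more. Another is to extend amber explicitly down to the red count. The choice of lower limit is the committee's, but it must be fixed in advance.
2. **Uses one denominator** in all three bands.
3. **States the actual recruitment window and gives matching counts for every band.** With the first option and a 20-month window (an assumption), these would be red below 40, amber 40 to 59 and green 60 or more. If green then falls short of the recruitment target, say so.

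As an editorial change, write the amber bands as 50% to <70% for engagement and 30% to <70% for retention.

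The cost is a rewording of one table with TSC sign-off. Sample size, data collection and analysis do not change.

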Prospective participants will be identified through Early Detection and Intervention Teams (EDIT) and Early Intervention for Psychosis (EIP) services at three UK National Health Service (NHS) mental health trusts in the North West of England, and other mental health services that interface with EDIT/EI services and provide support to individuals who may meet ARMS criteria (e.g., student mental health services; complex primary care psychological therapy services, etc.). ARMS individuals who participated in recent non‐interventional studies by the research team and consented to further contact for research involvement purposes will also be approached. Trained RAs will obtain informed consent prior to an eligibility assessment using the CAARMS‐23 and the TALE.

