#### Randomisation and Allocation Concealment

3.2.1

Participants will be randomly allocated to either (1) EMDR+TAU, (2) TF‐CBT+TAU, or (3) TAU only at a ratio of 1:1:1. Randomisation will be independent and concealed via an online pseudo‐random list with random permuted blocks of varying sizes. Allocation will be concealed from the RAs conducting follow‐up assessments. If an RA becomes “unblinded” to a participant's allocation during the study, where possible, the participant will be allocated to another RA. Where this is not possible, interview‐based measures will be recorded with participant consent, and the measure will be scored by blinded RAs.

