## Feasibility RCT Analysis

6

Descriptive statistics will be used to document participants' flow in the trial in accordance with all relevant fields of the CONSORT statement extension for feasibility trials (Eldridge et al. 2016). These will include: the number of referrals received per month, the source of recruitment, number of participants contacted, number of participants assessed for eligibility, number of participants consented into the trial (and reasons for non‐eligibility or withdrawal of interest, when appropriate and where given), number of participants allocated to each RCT arm (and those who did not receive the treatment allocated as intended), and the number of participants retained at the 9‐month follow‐up assessment. Furthermore, descriptive analyses of EMDR and TF‐CBT engagement data (number of sessions received by participants allocated to the EMDR+TAU and TF‐CBT + TAU arms) and fidelity data (therapy session records forms data as well as EFRS and CTS‐R data) will be conducted to estimate fidelity/adherence of the interventions received by study participants.

To examine the acceptability of assessment measures administered as part of the trial and the viability of extracting transition information and concomitant treatment data from clinical notes, all measures will be examined for completeness and reasons for missingness. There will be no formal hypothesis testing comparing the three groups for clinical effectiveness; however, summary statistics (Mean, SD, % of missing data) will be tabulated for each quantitative measure by trial arm at each time point, and unadjusted mean differences between the arms at the 9‐month follow‐up and their associated 80% CI will be calculated to provide some evidence towards the promise of efficacy of the interventions considered in this feasibility trial and inform the design of the future definitive trial (Lee et al. 2014).

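### Transition to psychosis has clinical notes as its only named source, and the planned check on that source cannot reveal a transition the notes never recorded

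*Protocol article*

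**What the plan says.** The protocol article names one source for transition. The abstract states: "Clinical notes will be reviewed to identify transitions to first episode psychosis up to 12 months". Section 3.1 (Design) says that the 12-month outcomes come from screening medical records. Section 5 (Outcomes) repeats that "clinical notes will be screened to assess transition rates to first episode of psychosis".

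Section 6 (Feasibility RCT Analysis) sets out to examine "the viability of extracting transition information and concomitant treatment data from clinical notes", and the method it gives is that "all measures will be examined for completeness and reasons for missingness". It describes no comparison with a second source.

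Transition is defined only in Table 1, as an exclusion criterion. There it is "operationally defined as meeting CAARMS transition criteria" (a psychotic episode of at least a week, whether treated or not), and/or antipsychotic treatment above a stated level. The article does not carry this definition over to the outcome.

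Table 3 schedules the CAARMS-23, described as an "interview to identify those at ultra‐high risk of developing psychosis", at baseline and at 9 months. Section 3.2.1 covers blinding: "Allocation will be concealed from the RAs conducting" follow-up assessments, with blind scoring of recorded interviews as a fallback.

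**The concern.** A check on completeness and missingness finds absent values, and a missed transition is not an absent value. If the notes are available, are read and contain no record of an episode, the natural coding is a complete negative. The article states no coding rule, so this is an inference, but it is hard to see another outcome. Notes could score perfectly on the planned check and still miss transitions.

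The definition in Table 1 makes this more than theoretical. An untreated episode counts as transition at entry, and an untreated episode is the kind least likely to reach a clinical record. Recruitment also extends to "other mental health services that interface with EDIT/EI services and provide support to individuals who may meet ARMS criteria", so participants may not all be followed by specialist early-detection or early-intervention teams.

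Two things are at stake: the transition rates this trial reports, and what it can say about notes as an endpoint source. The abstract's conclusions name fewer transitions as a possible gain from these therapies, so the definitive trial may well depend on this outcome. As written, the trial would pass on a verdict about whether notes can be extracted, with no evidence on whether they are right.

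**Working it through.** The article gives no transition rate, notes sensitivity or expected event count, so there is no stated figure to reproduce. The logic comes first, then an illustration of scale.

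**What each check can see**

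| True state | Notes | Recorded value | Seen by completeness/missingness check? | Seen by comparison with 9-month CAARMS-23? |
|---|---|---|---|---|
| Transition | Not available | Missing | Yes | Yes, if attended and onset by 9 months |
| Transition | Read, no episode recorded | Complete negative (inferred) | No | Yes, if attended and onset by 9 months |
| Transition | Episode recorded | Positive | Not a problem | Confirms |

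The second row is the gap.

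**Inputs**
- N = 70 (abstract) or 75 (section 3.2). The article gives both, and the choice does not affect the conclusion.
- 9-month retention of 70%, the threshold in Table 2 for demonstrated feasibility.
- Assumed, not in the article: 12-month transition p of 5% to 20%, and notes sensitivity Se of 60% to 80%.

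**Missed transitions: N × p × (1 − Se)**
- N = 75, p = 0.10, so 7.5 true transitions.
- Se = 0.80: 7.5 × 0.20 = 1.5 missed; observed rate 0.10 × 0.80 = 8%.
- Se = 0.60: 7.5 × 0.40 = 3.0 missed; observed rate 0.10 × 0.60 = 6%.
- Smallest case: 70 × 0.05 × 0.20 = 0.7. Largest case: 75 × 0.20 × 0.40 = 6.0.

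**Chance of at least one miss: 1 − (1 − p(1 − Se))^N**
- N = 75, p = 0.10, Se = 0.80: 1 − 0.98^75 = 78%.
- N = 75, p = 0.10, Se = 0.60: 1 − 0.96^75 = 95%.

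**What the 9-month CAARMS-23 could add**
- Participants with both sources at 70% retention: 0.70 × 70 = 49, or 0.70 × 75 = 52.5.
- True transitions among them, if all occurred by 9 months: 49 × 0.05 = 2.45 up to 52.5 × 0.20 = 10.5. If three quarters occurred by then (assumed): about 1.8 to 7.9.
- Exact (Clopper-Pearson) 95% intervals for notes sensitivity: 4 of 5 gives 28% to 99%; 8 of 10 gives 44% to 97%.

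The comparison can therefore expose individual missed cases, but it cannot estimate sensitivity with useful precision.

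**The case against.** The strongest reply is that this is a condensed article. Notes screening is introduced as an addition to the 9-month battery, and nothing says the CAARMS-23 will not be scored for transition. Coding rules and the combining of sources commonly sit in a full protocol or analysis plan that is not shown. Other 9-month information, such as updated diagnosis and medication, could also reveal transitions.

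Part of this stands. A reader might infer that the plan excludes the CAARMS-23 from counting transitions. The article does not say so; it simply states no such use. But the point does not rest on silence alone. The article names the source, says it will examine whether extraction is viable and names the check, and that check cannot detect a false negative.

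A reader might also infer that notes are fuller in the therapy arms, so that therapy would falsely appear to have more transitions. The two therapy arms do have up to 24 extra sessions and sessional symptom measures, so unequal capture is plausible. But nothing in the article says that session records enter the clinical notes, or that notes are thinner for any recruitment route. The direction and size of any imbalance are assumptions. Nor does the article say who screens the notes, so unblinded judgement of transition cannot be inferred.

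The reply is also right about consequences. Transition is not among the four progression criteria in Table 2, and section 6 rules out formal testing of clinical effectiveness between the arms.

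**Conclusion.** The point holds as a limited one. Notes are the only source named for transition, and the stated check on them cannot show transitions they omit. The article states no use of the blinded 9-month CAARMS-23 to fill or test that gap.

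The size is illustrative. At 75 participants and an assumed 10% true rate, notes sensitivity of 60% to 80% would lose 1.5 to 3.0 of 7.5 transitions and lower the observed rate to 6% to 8%. Over the wider assumed ranges the expected loss runs from 0.7 to 6.0. None of these inputs comes from the article.

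No decision rule in this feasibility trial changes. What changes is how far its transition rates, and its conclusion about notes as an endpoint source, can be relied on when the definitive trial is designed.

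**What to change.** - State the outcome definition of transition, and apply the CAARMS transition criteria to the 9-month CAARMS-23. Settle this before those interviews are scored.
- Report CAARMS-23-met and notes-documented transition separately, by arm.
- Among 9-month attenders, cross-tabulate the two sources for the period up to 9 months. Review every discordant case descriptively, in both directions, and use the result to inform the choice of ascertainment method for the definitive trial.
- Do not make an estimate of notes sensitivity a progression criterion. With roughly 2 to 10 events it would be a go/no-go rule resting on very little information.
- If a combined rate (either source positive) is wanted, show it only beside the separate sources, because it depends on who attends at 9 months.

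The cost is a small extra analysis of data already scheduled for collection. The limits are that months 9 to 12 have no CAARMS check, and neither do participants lost to follow-up, who could be up to 30% even when the retention criterion is met.
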